**Figure 4 F4:**
[figure not shown]
Electroacupuncture performed at GB33, GB34, SP9, and SP10 acupoints by transcutaneous electrical nerve stimulator.

After treatments in each session, a designated physician will record the frequency of analgesic used, the VAS during rest and activity, the response to our therapy, and any adverse events. The patients can receive analgesics during the treatment period; however, they will be prohibited from receiving other acupuncture, rehabilitation program or knee surgery in any other clinic. If the patients do not follow these provisions, we will exclude these patients from our study protocol. On successful completion of 12 sessions, all participants will be subjected to the same exam and questionnaire as during the pretest.

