### Outcome measurements

2.6

We will evaluate the KOA patients with subjective tests and objective questionnaires at the beginning of the treatment and after 12 weeks of therapy. The data will be collected and entered into the patient's medical record in a computer, and all patient-related documents will be securely stored. Only the study-related investigators, including the physicians and the assistants will be allowed to access to the trial dataset. The primary outcomes will be the difference in the frequency of analgesic used and VAS scores during rest and activity between the treatment group and the control group. The secondary outcomes will be the difference between the control and treatment groups in terms of WOMAC, KOOS, body composition analysis, knee range of motion test, quadriceps muscle stiffness, one-leg standing with eyes open test, and the 30-s chair stand test after completing the 12 sessions of treatments.

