
The reason for patients who are not completing the follow-up visit or dropping out of this study, such as adverse events, suboptimal response to therapy, failure to return for following up, and refusal to receive treatment will be recorded. The potential adverse events will also be recorded although only 6 J/acupoint will be delivered to each acupoint.

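### Excluding patients who use prohibited care, and giving the post-test only to those who complete 12 sessions, can leave end-of-treatment outcomes selectively missing

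*Protocol article*

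**What the plan says.** The closing paragraph of section 2.5 (after Figure 4) permits analgesics during treatment, but of other care it says "they will be prohibited from receiving other acupuncture, rehabilitation program or knee surgery in any other clinic". The consequence of a breach is: "If the patients do not follow these provisions, we will exclude these patients from our study protocol". The next sentence sets the condition for the final assessment: "On successful completion of 12 sessions, all participants will be subjected to the same exam and questionnaire as during the pretest". According to the opening of section 2.5, that pretest covers analgesic frequency, VAS at rest and in activity, and all the secondary measures.

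The same closing paragraph also states: "After treatments in each session, a designated physician will record the frequency of analgesic used, the VAS during rest and activity". Section 2.6 defines the primary outcomes: "The primary outcomes will be the difference in the frequency of analgesic used and VAS scores during rest and activity". It compares the secondary outcomes once the 12 sessions are complete. For patients who leave, it says only that reasons "such as adverse events, suboptimal response to therapy, failure to return for following up, and refusal to receive treatment will be recorded".

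Section 2.7 names repeated-measures ANOVA and GEE for VAS and the secondary measures. It does not say which visits enter the models.

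Section 2.6 places the final evaluation "at the beginning of the treatment and after 12 weeks of therapy", whereas the abstract and sections 2.2 and 2.5 describe a 4-week course.

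**The concern.** A patient whose knee is still painful is the one most likely to look for other acupuncture, rehabilitation or surgery, or to stop attending. The exclusion trigger and the completion condition both occur after randomisation, and both are plausibly consequences of the outcome being measured. The protocol itself counts suboptimal response among the reasons for dropout.

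Because the arms differ by active versus sham laser, the rate of leaving, or its link with poor response, may differ between them. The patients who have a post-test would then no longer be comparable as randomised, and the estimated laser effect could be shifted either way. A post-test that was never taken cannot be recovered by any later analysis plan.

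**Working it through.** **1. What each rule removes.** A patient excluded or lost before session 12 does not meet the stated condition for the post-test.

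| Outcome | Recorded when | Left after early exit |
|---|---|---|
| WOMAC, KOOS, body composition, range of motion, stiffness, one-leg stand, chair stand | Pretest and post-test | Baseline only |
| VAS, analgesic frequency | Pretest, each session, post-test | Baseline and sessions up to exit |

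**2. The plan's own sample size (section 2.4).** Inputs: effect size 0.569, alpha 0.05, power 0.80, correlation 0.5, stated N = 22. Reading 0.569 as Cohen's f in the between-groups test of a repeated-measures ANOVA with m occasions, the noncentrality is λ = f²·N·m / [1 + (m − 1)ρ].

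With m = 2 and N = 22, λ = 0.3238 × 22 × 2 / 1.5 = 9.50, which gives power 0.834. At N = 20 power is 0.794. So 22 is the smallest balanced total, and it is reproduced with two measurement occasions. With 13 occasions the same formula gives 16. The planning figure therefore fits a pretest and post-test comparison, which needs the post-test.

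**3. Planning difference and SD (means and SDs in section 2.4).**
- Difference in change: (6.4 − 3.2) − (5.9 − 3.8) = 3.2 − 2.1 = 1.1.
- SD of change at correlation 0.5, treatment: √(1.9² + 1.7² − 1.9 × 1.7) = √3.27 = 1.81.
- SD of change, control: √(1.8² + 2.3² − 1.8 × 2.3) = √4.39 = 2.10.
- Pooled: √[(3.27 + 4.39)/2] = 1.96.

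**4. Selection bias.** Assume that a latent tendency to leave has correlation r with poor response, and that the fraction d with the strongest tendency leaves. Mean improvement among those who stay is then too high by r × SD × k(d), with k(d) = φ(z₁₋d)/(1 − d). The values are k(0.10) = 0.195, k(0.15) = 0.274, k(0.20) = 0.350, k(0.25) = 0.424 and k(0.30) = 0.497. Bias in the treatment-minus-control difference is r × 1.96 × [k(d treatment) − k(d control)].

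| Loss, treatment / control (20% overall) | r = 0.3 | r = 0.5 | r = 0.7 |
|---|---|---|---|
| 20% / 20% | 0 | 0 | 0 |
| 15% / 25% | −0.09 | −0.15 | −0.20 |
| 10% / 30% | −0.18 | −0.30 | −0.41 |

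Simulation agreed to within 0.01. The overall 20% is the dropout rate in section 2.4; the splits and r are assumptions. Negative values shrink the apparent laser benefit, and swapping the arms reverses the sign. The zero row needs the same r in both arms as well as equal loss.

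**5. Type I error.** With no true effect, 25 per arm, 10%/30% loss and a two-sided t test on those who remain, simulation (5,000 replicates) gave 0.072 at r = 0.5 and 0.108 at r = 0.7. With 20%/20% loss it gave 0.053 and 0.048.

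**6. What the named methods do.** Repeated-measures ANOVA as usually run drops patients with an incomplete record. GEE can use the session records, but unweighted it needs loss unrelated to outcome, which is the assumption in doubt.

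**The case against.** Four points on the other side have weight.

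- **The primary outcomes are not measured only at the end.** A reader might infer that the primary comparison becomes a completer analysis. The documents do not support that in general: VAS and analgesic use are recorded at every session, and GEE is named. The label is strictly right for the pre/post comparison, for repeated-measures ANOVA with incomplete cases dropped, and for the secondary outcomes.
- **The exclusion sentence does not say that collected data are deleted.** It can be read as ending study participation, and an analysis set is commonly defined in an analysis plan that is not shown. This stands, so the absence of an intention-to-treat statement is not the point. What remains is that the stated rules stop collection of the post-test under either reading.
- **The bias may be small.** Analgesics are allowed, the course is short, and nothing says how often prohibited care occurs. With loss equal and equally outcome-related in both arms, bias is near zero.
- **Larger figures are one unfavourable split.** Suppose 5 of 25 sham patients leave at r = 0.5, active-arm loss is random, and the VAS SD is 1.94. The shift is then about 0.33 points, or 30% of 1.1; with 7 of 25 it is about 0.44 points, or 40%. The arithmetic is right. But the first case spends the whole planned 20% sham-arm loss on outcome-related exits, and the second exceeds it.

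**Conclusion.** The concern holds in a limited form. Two stated rules in section 2.5 can make end-of-treatment values go missing in a way related to outcome. The secondary outcomes and the pre/post comparison of VAS and analgesic use are fully exposed. For the primary outcomes, the session records and GEE reduce the exposure without removing it.

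The size is unknown. Under the assumptions shown it runs from near 0 with equal loss to about 0.4 VAS points (0.41/1.1 = 37% of the planning difference) at 10%/30% loss with correlation 0.7. The direction depends on which arm loses more poor responders.

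The plan should be changed on this point. The protocol does not support the stronger conclusion that the primary result is invalid, or that a bias of a particular size is to be expected.

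**What to change.** Replace the exclusion sentence in section 2.5 with wording such as:

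> Patients who receive prohibited care are recorded as protocol deviators; their outcome data are kept and their outcome assessments continue. All randomised patients are invited to the post-test at the planned end-of-treatment time whatever the number of sessions attended, and are analysed in the group to which they were randomised, with per-session VAS and analgesic records included. An analysis without deviators is a sensitivity analysis.

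This concerns outcome collection and analysis only. It does not say whether study treatment continues after prohibited care. Because the wording relies on a fixed end-of-treatment time, the 4-week and 12-week statements must be reconciled in the same amendment.

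The cost is an amendment, the effort of bringing non-completers back for one visit, and slight dilution of the effect by patients who did not adhere. The gain is mainly less bias. Analysing 50 patients instead of 40 (20% lost) moves power only from 0.982 to 0.995 under the plan's own model, or from 0.44 to 0.52 if 0.569 is read as a standardised mean difference.

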### Outcome measurements

2.6

We will evaluate the KOA patients with subjective tests and objective questionnaires at the beginning of the treatment and after 12 weeks of therapy. The data will be collected and entered into the patient's medical record in a computer, and all patient-related documents will be securely stored. Only the study-related investigators, including the physicians and the assistants will be allowed to access to the trial dataset. The primary outcomes will be the difference in the frequency of analgesic used and VAS scores during rest and activity between the treatment group and the control group. The secondary outcomes will be the difference between the control and treatment groups in terms of WOMAC, KOOS, body composition analysis, knee range of motion test, quadriceps muscle stiffness, one-leg standing with eyes open test, and the 30-s chair stand test after completing the 12 sessions of treatments.

We will evaluate the frequency of analgesic used to treat knee pain after each intervention, including acetaminophen, a non-steroidal anti-inflammatory drug, or opioid drug. VAS will be used to evaluate the intensity of knee pain during activity and rest on a scale of 0 to 10, corresponding to the minimum and maximum discomfort intensity. The minimal clinical important difference (MCID) of VAS is 1.8 units,^[34]^ implying that an effective treatment will improve the VAS score by 1.8 points. WOMAC is a subscale for assessing the physical function of knee joints. There will be 17 questions with grading from 0 to 4 points for each question. Thus, the total score will be between the ranges of 0 to 68 points. Higher points correspond to more difficulties in performing a given activity. The MCID of WOMAC is 6 units.^[35]^ The KOOS is a self-administered scale and evaluates five outcomes, including pain, symptoms, activities of daily living, sport and recreation function, and knee-related quality of life. The scale is divided into five factions, including none, mild, moderate, severe, and extreme, which represent the severity of the deterioration of knee function and the impairment in daily living.^[36]^ A previous study showed that one-time LLLT had some effects on improving the knee function and muscle strength of quadriceps in KOA.^[37]^ We use Myoton-3 myometer and InBody 270 to measure muscle functions. In Myoton-3 myometer, the tip is placed on the midpoint of the patient's rectus femoris to measure muscle stiffness, representing the muscle ability to resist the changes of its shape, caused by external forces.^[38]^ InBody 270 can measure body composition, including the fraction of muscle and fat, and the muscle mass distribution of four limbs. This device will be used to evaluate the composition of thigh muscles and any possible muscle imbalance. One-leg standing with eyes open test will be used to assess balance and muscle strength of lower extremities.^[39]^ The patient will stand on one leg with their hands on hips and eyes opening for up to 120 s. We will record the time that the patient can stand on one leg under the instruction. Another functional assessment is the 30-s chair stand test, which can evaluate the muscle performance and the endurance of lower limbs.^[40]^ The patient will sit on the chair with bilateral feet stepping on the ground and hands crossed over the chest. Subsequently, the patient stands up and then sits down. Completing one standing up and then sitting down scores one, etc. We will calculate the number of times the patient can stand up and then sit down in 30 s. A designated study assistant will evaluate these tests.

The reason for patients who are not completing the follow-up visit or dropping out of this study, such as adverse events, suboptimal response to therapy, failure to return for following up, and refusal to receive treatment will be recorded. The potential adverse events will also be recorded although only 6 J/acupoint will be delivered to each acupoint.

### Statistical analysis

2.7

All data will be presented in the form of mean ± standard deviation. The independent *t* test and chi-square tests will be used to assess and compare the baseline patient characteristics between the treatment and the control groups. Repeated measure analysis of variance and the generalized estimating equation will be used to evaluate changes in the VAS, WOMAC, KOOS, body composition, knee range of motion, rectus femoris stiffness, standing on one foot, and 30-s chair stand test between the treatment and the control groups. Statistical significance will be considered at a *P*-value of <.05. All statistical analyses will be performed with the SPSS for Windows, version 26 (Statistics 26, SPSS, IBM Corp., Chicago, IL).

### Data monitoring

2.8

The IRB and Kaohsiung Chang Gund Memorial Hospital's statisticians will be a part of the data monitoring committee in this study. LA and EA are general practices. LA is a routine intervention and non-invasive treatment. The common side effects of EA are subcutaneous bleeding, pain, fainting during acupuncture treatment, while in very rare cases, serious complications such as pneumothorax or septicemia are possible.^[41]^ However, since the designated acupuncture physicians are well trained in aseptic acupuncture procedures and proficient in human anatomy, the risk of serious complications is minimal. Additionally, the risk of fainting during the EA treatment will be extremely low because, in the study setting, the patient will be treated in a supine position.

## Discussion

3

The prevalence of KOA in 50 years or older population is about 37% in Taiwan. This frequency is expected to increase, as Taiwan has a large number of elderly adults.^[2,42]^ According to Taiwan's National Health Insurance Research Database, the frequency of KOA patients requiring total knee replacement has increased between 1996 and 2010. Also, the cost associated with total knee replacement has increased from $39.69 to $83.35 million.^[42]^ As such, it is important to identify cost-effective therapy for KOA; EA and LA are known cost-effective analgesic treatments.^[26,43]^

Berman et al conducted a large randomized controlled trial study in 2004, which recruited 570 KOA patients and showed that EA had positive effects on improving knee function and relieving pain in KOA patients.^[19]^ EA cannot only alleviate pain and improve stiffness and disability, but also lead to a significant rise and fall in plasma beta-endorphin and plasma cortisol, respectively, after 10 sessions of treatment. Collectively, these effects could be the underlying analgesic mechanism of EA.^[44]^ This hypothesis is further validated by the fact that EA with etoricoxib was more effective than either placebo plus etoricoxib or etoricoxib alone in addressing KOA symptoms.^[43]^ Recently, a systematic review suggested that the therapeutic sessions of EA for at least 4 weeks significantly improved the VAS, WOMAC, and Lysholm knee score scale (LKSS).^[45,46]^ A detailed literature review on the application of EA in KOA patients, including treatment frequency and assessment, is listed in Table 1.

**Table 1 T1:**
[figure not shown]
Literature review on the effectiveness of electroacupuncture or laser acupuncture in knee osteoarthritis.

A double-blind, randomized control trial in 1994 used a low power Ga–Al–As laser treatment in KOA patients at a frequency of 3 times per week for 3 weeks and showed that there was no difference in results between the treatment group and the control group.^[47]^ The study concluded that a placebo effect was observed since the symptoms improved before and after interventions in both the treatment group and the control group.^[47]^ Another double-blind, randomized trial in 2004 with LLLT (50 mini-watt, 830 nm, and output energy of 1.5 or 3 J/point) at a frequency of 10 times in 2 weeks showed that there was no significant improvement in VAS and WOMAC parameters between the treatment group and control groups.^[48]^ A meta-analysis showed that LA had some positive effects on the WOMAC parameter in KOA patients; however, insufficient information on wavelength, energy density, and treatment duration made results’ interpretation difficult.^[49]^ In a recent meta-analysis, LLLT at a strength of 4 to 8 J and 785 to 860 nm wavelength with the mean duration of the treatment periods 3.53 weeks was found to reduce pain and disability in KOA patients after the end of therapy and during follow-ups 3 months.^[28]^ The multi-focal LLLT on quadriceps had shown not only analgesic effect but also improved function and muscular strength in KOA patients.^[37]^ The reasons that these studies exhibited ambiguous results may be the differences in laser dosage, laser power density, the treatment sites, and the treatment frequencies.^[50]^

Among many of the mechanisms of KOA, synovial inflammation (synovitis), abnormal bone structure, osteophytes, and bone marrow lesions can result in knee pain.^[5]^ It is possible that EA treatments could lead to activation of the nervous system and inhibition of inflammatory and neuropathic pain by desensitizing peripheral nociceptors and reducing pro-inflammatory cytokines.^[51]^ The clinical effects of LA are likely to encompass anti-inflammatory, neural modulation, cell healing and regeneration effects.^[23]^ Both LA and EA have anti-inflammatory and neural modulation, which may decrease knee pain in KOA. Conversely, exercise therapy can reduce knee pain in patients with KOA and these exercise therapies are focused on improving aerobic capacity and quadriceps muscle strength.^[17]^ LA has an analgesic effect and can improve the function and muscle strength of quadriceps in KOA.^[37]^ Besides, LA and EA have many advantages, including low risks of complications, pain, cost, and high analgesic efficacy. Although some studies confirmed such beneficial effects of LA or EA in improving KOA symptoms, the combined effect of EA and LA on KOA remains elusive.

In this study protocol, we will use LA at 6 J/acupoint delivered with an 810 nm laser in addition to EA treatment for 4 weeks. LA treatments are poised to heal damaged chondrocytes, which are more susceptible to pain stimulation.^[59]^ The outcome evaluations will include analyses of subjective symptoms, quadriceps muscle functions, and body composition measurements. In conclusion, we hypothesize that a combination of LA and EA is expected to be more effective than these therapies alone in alleviating knee pain and stiffness and increasing muscle strength of lower limbs, which can further improve the balance and quality of life. Moreover, this combined therapy may also benefit in reducing the need for total knee replacement therapy and further decrease the cost coverage of national health insurance.
